### GWAS approach

Previous experience has learned that the use of candidate gene approaches (i.e. having a specific hypothesis for a specific piece of genetic variation) is a good strategy for disorders with a known pathophysiology, but is insufficient to identify genetic variation for complex disease phenotypes. With a few exceptions, such as Huntington's disease or Parkinson's disease, most phenotypes relevant for the field of neuropsychiatry are considered complex, heterogeneous and of multifactorial causality. Furthermore, their genetic origin is most likely the result of a combination of a large number (>200) genetic variants, each with small effect sizes (Odds ratios around 1.1).

With the advent of new technology that allows to determine sequence variation in about one million genetic markers simultaneously (of the in total approximately 3 million genetic markers that vary between persons), genome-wide association studies (GWAS) have become a new, hypothesis-free research strategy that is especially suited to determine the genetics of complex phenotypes. The use of GWAS in other fields of medicine has resulted in the identification of multiple genetic markers associated with complex phenotypes. For example, more than ten polymorphisms have now been associated with diabetes mellitus type 2, most of which were unknown from candidate gene approaches. GWAS in addition allows for the identification of copy number variants (CNVs), for example deletions, insertions, duplications and complex multi-site variants, that have been shown to be involved in the aetiology of psychiatric disorder.

The drawback of GWAS approaches is that they require huge samples, usually in the order of 20.000 to 60.000 or more subjects, given the degree of multiple testing that needs to be corrected for and the anticipated small effect sizes. Therefore, multi-site international collaboration is the only means to acquire these sample size requirements and MHeNS ascribes to the scientific policy of worldwide sharing of data in order to elucidate the causes of complex disorders. This policy is also mandatory for recipients of funding from the EU, Wellcome Trust, NIH, NIMH, etc. GWAS data collection in

MHeNS is therefore shared anonymously with the various international scientific consortia that study the genetics of schizophrenia, bipolar disorder and other phenotypes and workers of MHeNS are usually involved in the analyses of these data.

#### Hypothesis-based approach

Since the GWAS research strategy is able to identify small genetic effects on complex phenotypes, but is not able to demonstrate how newly identified *specific* genetic markers contribute to the disease phenotype, a complementary approach is also needed. This complementary approach is hypothesis-driven involving specific genetic variation, aiming to unravel the genetic contribution of novel identified variants to the disease phenotype. Since insights concerning relevant polymorphisms and haplotypes change rapidly, an up-to-date relational (i.e. cross-relating genotype, phenotypic expressions, biochemical pathways) database relevant for the neurosciences is maintained within MHeNS. The mainly replicatory genetic analyses thus are always matched against the most recent information available worldwide. The scientific approach of GWAS identification followed by hypothesis-based replication also represents a tightly organised international effort: one group identifies a novel variant, followed by immediate efforts to replicate by international groups.

#### DNA analysis

Therefore, each person's complete set of DNA, or genome, is purified from the blood or cells, placed on tiny chips and scanned on automated laboratory machines. The machines quickly survey each participant's genome for strategically selected markers of genetic variation (around 1 million), which are called single nucleotide polymorphisms, or SNPs. Since information relating to 1 million SNPs is difficult to relate conclusively with any complex phenotype by a single research group, anonymized data will be shared within the framework of international consortia. Secondly, since insights concerning relevant markers change rapidly, the DNA of these individuals is stored for 15 years for determination of previously undetermined genetic markers when there is new information that these markers may be relevant to the phenotype studied.

#### **7.1.3 Other study parameters (if applicable)**

Possible moderators of main study parameter:

- number of previous depressive episodes

- previous stress exposure, measured with the Childhood Trauma Questionnaire and the Interview for Recent Life Events
- personality, measured with the NEO personality inventory

Possible confounders/mediators:

- comorbidity (e.g. substance dependence, personality disorders)
- empowerment, measured with the Empowerment Questionnaire
- medication (type, duration of use)

## 7.2 Randomisation, blinding and treatment allocation

Patients are randomly divided into the 'MET-D intervention *with* feedback' group, the 'MET-D intervention *without* feedback' group and the 'control' group.

Randomization takes place after screening procedures.

Subjects are obviously not blind to their treatment allocation, however, they do remain blind as to how ESM measures relate to testing the hypothesis. Since MET-D feedback will be given to the therapist as well, the therapist is also not blind to the treatment allocation.

In order to check that the HDRS ratings by the researcher are not biased by the researcher's knowledge of the participant's condition, we compare IDS scores with HDRS ratings. The IDS is a self-report measure with similar item content compared to the HDRS and is proven highly related to clinician's rated HDRS score.

## 7.3 Study procedures

Subjects are screened for the inclusion criteria, by means of the SCID-I and answer a questionnaire concerning demographic variables. After inclusion subjects:

- undergo a psychiatric interview: HDRS
- fill out additional questionnaires concerning personality (NEO-PI), depression symptomatology (IDS), trauma (Childhood Trauma Questionnaire and Recent Life Event Scale), empowerment (Empowerment Questionnaire), illness and costs due to loss productivity (PRODISQ), illness and illness related costs (TiC-P), and quality of life (Euroqol-5D).
- spit some saliva in special tubes as to measure polymorphisms/haplotypes in the DNA that have been associated in previous studies with the brain reward system and depression.

At base-line:

All subjects will participate in a 5-day MET-D measurement period. After this period, they undergo 2 psychiatric interviews (the depression part of the SCID-I and the HDRS) and

have to complete one self-report questionnaire concerning depressive symptoms (IDS). Subjects are briefed and de-briefed after the ESM period. The ESM debriefing includes the collection of the MET-D devices and discussion concerning unclarities or missing values. See also 'study design' for a more elaborate description.

The intervention period:

Subjects randomized to the 'MET-D intervention *with* feedback' group will participate in a 6-week-period of 3 days a week of ESM (collected by the MET-D) and receive weekly feedback on these measurements. Subjects randomized to the 'MET-D intervention *without* feedback' group will also participate in a 6-week-period of 3 days a week of ESM (collected by the MET-D), but no feedback on the daily recordings is given. In order to prevent any effects of different duration of researcher contacts in both groups, the difference in time is filled by doing two more weekly interviews on anxiety and depression in the 'MET-D intervention *without* feedback' group.

All subjects receive TAU as well during the intervention period.

After the intervention period:

All subjects will participate in a second 5-day ESM period, and are again briefed and debriefed with respect to this procedure. Before and after the 5-day ESM period, all subjects again undergo the psychiatric interviews (the depression part of the SCID-I and HDRS) and have to complete the self-report questionnaire concerning depressive symptoms (IDS). The Empowerment Questionnaire has to be completed by all subjects before the 5-day ESM period as well.

Follow up period:

For all subjects, follow-up measurements of SCID-I and HDRS take place at 4, 8, 12 and 24 weeks after the end of the intervention. The follow-up of the Recent Life Event Scale will take place at 12 weeks after the intervention. The follow up of TiC-P, PRODISQ, and EQ-5D will take place at 12 and 24 weeks after the intervention.

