Levels of reward experience, stress sensitivity and affect variability are calculated from the MET-D observations for each subject at the end of each intervention week. Since these are complex phenotypes derived from combinations of data they are not subject to easy conscious manipulation by patients.

Before entering the study, subjects will be screened for a current depressive episode by means of the Structured Clinical Interview for DSM-IV Axis I Disorders (SCID-I) and the Hamilton Depression Rating Scale (HDRS). After inclusion, a saliva sample will be taken for genetic analysis and the subject has to complete the following measurements: Inventory of Depressive Symptoms (IDS) [31], the NEO personality inventory (NEO-PI-R) [32, 33], Childhood Trauma Questionnaire (CTQ) [34], Interview for Recent Life Events (IRLE) [35], Empowerment Questionnaire [36], TiC-P (Trimbos/iMTA questionnaire for Costs associated with Psychiatric Illness) [37], PRODISQ (PROductivity and DISease Questionnaire) [38], and EQ-5D (Euroqol-5D) [39]. Because we hypothesize that the effect of the MET-D feedback on reward experience results in an increase in of empowerment of the subjects, the Empowerment Questionnaire will be used as an additional measurement of the effect of the MET-D intervention. The latter three questionnaires (TiC-P, PRODISQ and EQ-5D) will be used in the costs-efficacy analysis of the MET-D.

All subjects receive additional MET-D training on a separate moment. All groups receive the following pre and post intervention measurements: i) SCID-I interview for diagnosis of depression, ii) HDRS, and iii) IDS. In addition, there are four follow-up measurements of SCID, HDRS and IDS for all groups at 4, 8, 12 and 24 weeks after the end of the intervention, and two follow up measurements of TiC-P, PRODISQ, and EQ-5D for all groups at 12 and 24 weeks after the intervention (see table 1).

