## 7. METHODS

### 7.1 Study parameters/endpoints

#### 7.1.1 Main study parameter/endpoint

The main objective is to examine if feedback on relevant daily life person-context interactions (reward experience and affect variability as measured with MET-D) during pharmacotherapy results in an immediate and follow-up decrease of depressive symptomatology and relapse and whether this leads to a reduction in health care consumption and costs. Main outcomes therefore are pre – post intervention change in i) depressive symptomatology, ii) ESM phenotypes (reward experience and stress sensitivity), iii) pre – post intervention change on the empowerment questionnaire, and iv) health care consumption and costs. This economic evaluation will involve a combination of a cost-effectiveness analysis (CEA) and a cost-utility analysis (CUA). In a CEA effects are presented in clinical outcomes (in our study decrease depression and relapse). The primary outcomes measure for the cost-utility analysis will be Quality Adjusted Life Years (QALYs), based on the EuroQol utility scores.

Furthermore, to examine whether the effect of the MET-D intervention with feedback leads to a long-term change in above described parameters depressive symptomatology, ESM phenotypes and health care consumption and costs are compared between the three groups on base-line and at 12 and 24 weeks follow up.

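### No EQ-5D, TiC-P or PRODISQ is scheduled between inclusion and 12 weeks after the intervention, so QALYs over that stretch rest on a straight line and costs on unstated recall windows

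*Protocol*

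**What the plan says.** **Schedule.** Section 7.3 has the PRODISQ, TiC-P and EQ-5D completed after inclusion, and then: "The follow up of TiC-P, PRODISQ, and EQ-5D will take place at 12 and 24 weeks after the intervention". Section 3 agrees, giving "two follow up measurements of TiC-P, PRODISQ, and EQ-5D for all groups at 12 and 24 weeks after the intervention".

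**End of the intervention.** Section 3 states: "All groups receive the following pre and post intervention measurements: i) SCID-I interview for diagnosis of depression, ii) HDRS, and iii) IDS". Section 7.3 has patients interviewed and completing the IDS both before and after the second 5-day ESM period, and adds one further instrument: "The Empowerment Questionnaire has to be completed by all subjects before the 5-day ESM period as well". Neither section names an economic instrument there.

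**Outcomes.** Section 7.1.1 introduces the main outcomes as pre-post changes. The fourth item is "iv) health care consumption and costs". On the cost-utility analysis it says: "The primary outcomes measure for the cost-utility analysis will be Quality Adjusted Life Years (QALYs), based on the EuroQol utility scores". A separate paragraph on long-term change compares the groups on costs, among other measures, at baseline, 12 and 24 weeks.

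**The concern.** Objective 1 (Section 2) expects an immediate effect on symptoms as well as a lasting one. The post-intervention visit is where an immediate effect on quality of life would show, and the EQ-5D is not taken there. Two utility values about 18 weeks apart cannot show whether a gain came early, came late, or came and went.

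Costs raise a similar question. Section 3 lets the therapist adjust strategy or advice in response to the feedback, so care use may change during the six intervention weeks. Whether those weeks are captured depends on how far back the questionnaires look.

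At stake is Objective 2, the economic evaluation, and mainly its cost-utility part. An analysis plan can define how to interpolate, but it cannot recover a measurement that was never taken.

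**Working it through.** The protocol gives no figure that depends on this schedule, so there is nothing to reproduce. The check is timeline arithmetic.

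**Inputs from the protocol.** The intervention lasts 6 weeks (Section 3). Economic instruments are completed at inclusion and at 12 and 24 weeks after the intervention (Sections 3 and 7.3). With week 0 as the start of the intervention and inclusion taken as about week 0, the measurements fall at weeks 0, 6 + 12 = 18 and 6 + 24 = 30. Counting the 5-day pre-period, the first gap is 18 + 5/7 = 18.7 weeks.

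**Assumptions, not in the protocol.** QALYs are the area under straight lines joining the measurements over 30 weeks. The between-arm utility difference is 0 at baseline and *d6*, *d18* and *d30* later, in units of the peak difference. The effect shapes are illustrative.

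**Formulas.**
- With a week-6 measurement: 6·*d6*/2 + 12·(*d6* + *d18*)/2 + 12·(*d18* + *d30*)/2 = 9·*d6* + 12·*d18* + 6·*d30*
- As planned: 18·*d18*/2 + 12·(*d18* + *d30*)/2 = 15·*d18* + 6·*d30*
- Shortfall of the planned schedule: 9·*d6* − 3·*d18*

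The shortfall is zero only when *d6* = *d18*/3, that is, when week 6 lies on the line from baseline to week 18.

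| Assumed shape | *d6*, *d18*, *d30* | Area with week 6 | Area as planned | Error |
|---|---|---|---|---|
| Linear build to week 18, held | 1/3, 1, 1 | 21 | 21 | none |
| Full by week 6, sustained | 1, 1, 1 | 27 | 21 | 6/27 = 22% too low |
| Full by week 6, half at 18, none at 30 | 1, 0.5, 0 | 15 | 7.5 | 7.5/15 = 50% too low |
| Full by week 6, gone by week 18 | 1, 0, 0 | 9 | 0 | 100% too low |
| Appears only after week 6 | 0, 1, 1 | 18 | 21 | 3/18 = 17% too high |

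**Absolute scale.** For an assumed peak difference of 0.10, the largest understatement is 9/52 × 0.10 = 0.017 QALY. The sustained shape gives 6/52 × 0.10 = 0.012 too low, and the late one 3/52 × 0.10 = 0.006 too high.

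**Costs.** A questionnaire at week 18 with a recall window of *r* weeks reaches back to week 18 − *r*. It covers *r* − 12 of the 6 intervention weeks, bounded by 0 and 6. A window of up to 12 weeks covers none, 13 weeks covers 1, and 18 weeks or more covers all 6. The protocol states no window.

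**The case against.** The case for leaving the plan alone has several sound parts.

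- **The intervention period is not missing from the QALYs.** A reader might infer that it is. Baseline and week 18 bracket it, and interpolation covers it. The result may be biased, but it is not absent, and with a linear build there is no bias.
- **The pre-post change in costs is not impossible to compute.** A reader might infer this from Section 7.1.1. But item iii repeats the pre-post phrase, so it need not govern item iv. The long-term comparison also matches the schedule exactly, and a baseline-to-12-week change is available. What stands is an ambiguity: if costs are a pre-post outcome in the sense used for symptoms and empowerment, no end-of-intervention value is scheduled.
- **Not every ratio is exposed.** The cost-effectiveness analysis takes depression and relapse as its effects. HDRS and SCID-I are recorded at the end of the intervention and at 4, 8, 12 and 24 weeks, so that effect side does not depend on the EQ-5D.
- **The cost gap is conditional.** With recall of 18 weeks or more, nothing is lost. The legend to the time-frame figure also lists a medication monitor with the SCID-I, HDRS and IDS, so some resource use may be recorded at the post visit.
- **The percentages are illustrative.** The shapes are straight between visits, so a week-6 measurement recovers the area by construction. In absolute terms the errors are small. How QALYs are built may be left to an analysis plan, and Section 9.2 writes the ICER in annual terms, not over 30 weeks.
- **The figure could not be checked.** The time-frame figure was not in the text reviewed, and the pre/post list in Section 3 is not exhaustive, since it omits the Empowerment Questionnaire. Even so, Sections 3 and 7.3 give the same economic schedule, and Section 3 counts two follow-up measurements.

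These points narrow the concern but leave its core: the text schedules no economic measurement for about 18 weeks, in a trial that expects an immediate effect.

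**Conclusion.** The point holds as a weakness of the measurement schedule. Utilities over the intervention and the following 12 weeks rest on interpolation between two values, and costs rest on unstated recall.

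Depending on the shape of the effect, the between-arm QALY difference could be anywhere from fully lost to 17% too high, with no error if the effect builds linearly. These figures assume straight-line area under the curve, a 30-week horizon and no baseline difference. The protocol does not show which shape applies.

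The consequence is limited to the cost-utility ratio and its acceptability curve and, if recall is shorter than about 18 weeks, to the cost side of both ratios. The clinical comparison of the arms is unaffected. The wording of Section 7.1.1 on costs needs clarifying but is not a proven contradiction.

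**What to change.** 1. In Sections 3 and 7.3, add the EQ-5D to one of the existing post-intervention visits, and preferably the TiC-P and PRODISQ too. Bring the time-frame figure into line. If the figure already shows these instruments at that visit, correct the text to match.
2. State the recall periods of the cost questionnaires, so that together they cover the time since the previous measurement.
3. Compute QALYs by area under the curve through baseline, post-intervention, 12 and 24 weeks.
4. If the cost questionnaires are not added, restate the cost outcome in Section 7.1.1 as baseline to 12 and 24 weeks.

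The cost is some extra questionnaire time at a visit already scheduled, and a protocol amendment. The protocol gives no completion times for these instruments, so the burden stated in the Summary and Section 10.4 would need updating.

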#### **7.4 Withdrawal of individual subjects**

Subjects can leave the study at any time for any reason if they wish to do so without any consequences. After consulting the independent physician, the investigator can decide to withdraw a subject from the study for urgent medical reasons. Subjects refusing collection of a saliva sample can still participate in the study if the wish to do so.

##### **7.4.1 Specific criteria for withdrawal (if applicable)**

Not applicable

**7.5 Replacement of individual subjects after withdrawal**

In case subjects withdraw before randomization, they will be replaced. After randomization they will not be replaced. By recruiting 20 participants more than the sample size chosen based on power calculations, we take a certain amount of drop-out into account.

**7.6 Follow-up of subjects withdrawn from treatment**

The number of withdrawals, and reasons for withdrawal will be reported in the publication of the study. It will be examined whether these subjects differ in any characteristics from those that do not withdraw.

**7.7 Premature termination of the study**

Not applicable.

**8. SAFETY REPORTING**

Not applicable

**9. STATISTICAL ANALYSIS****9.1 Descriptive statistics**

The categorical data (e.g. gender, education, employment status, marital status, type of TAU) will be analysed by frequency tables and chi-square tests. Means and standard deviations are used for continuous variables (e.g. age, number of previous depressive episodes).

**9.2 Univariate analysis**

ESM data (as measured with MET-D) have a hierarchical structure. This means that, multiple observations (beep level) are clustered within subjects (subject level). Multilevel regression analysis is suitable for this type of data because it takes the variability associated with each level of nesting into account [40]. The XT MIXED command in STATA 10.1 (Stata Corporation, College Station, Tex, USA) will be used to perform multilevel linear regression analyses. Analyses will be conducted conform previous work [3, 41-46] using multilevel random regression analyses. Technical details have been described in previous studies [3, 41-46]. As described in previous work [3, 41-46], the following positive affect/negative affect phenotypes of daily life emotional response patterns will be constructed from data collected with the Experience Sampling Method:

- i) positive affect (PA)
- ii) negative affect (NA)
- iii) instability of NA indexed by NA variability in daily life
- iv) instability of PA indexed by PA variability in daily life
- v) NA response to negatively appraised daily life events (stress-sensitivity)
- vi) PA response to positively appraised daily life events (reward experience)

First, to analyse the effect of feedback on immediate and follow-up depression scores and relapse we will compare relevant pre, post and follow-up variables between the three groups using multilevel regression analyses.

In addition, multilevel regression analyses are used to examine whether measurements of dynamic daily life person-context interactions (the above mentioned PA/NA affect phenotypes as measured with MET-D) significantly contribute to the prediction of future courses of depressive symptomatology.

Third, to examine whether individual differences in both the effect of feedback on daily life person-context interaction and the predictive value of these person-context interactions can be traced back to genetic differences, we will analyse the effect of genetic polymorphisms on pre, post and follow-up HDRS, SCID-I by means of multilevel regression analysis.

For the economic evaluation, the Incremental cost-effectiveness ratio (ICER) will be determined on the basis of incremental costs and effects of MET-D (with and without feedback) compared Usual Care. The cost-effectiveness ratio will be stated in terms of costs per outcome rate, the cost-utility ratio will focus on the net cost per QALY gained. The ICER will be calculated as follows.  $ICER = (C_i - C_c) / (E_i - E_c)$ , where  $C_i$  is the annual total cost of the MET-D (with and without feedback) group,  $C_c$  is the annual total cost of the Usual Care group,  $E_i$  is the effects at one year follow-up for the MET-D (with and without feedback) group and  $E_c$  is the effect at one year follow-up for the Usual Care group. The robustness of the ICER will be checked by non-parametric bootstrapping (1000 times) [47]. Bootstrap simulations will also be conducted in order to quantify the uncertainty around the ICER, yielding information about the joint distribution of cost and effect differences. The bootstrapped cost-effectiveness ratios will be subsequently plotted in a cost-effectiveness plane, in which the vertical line reflects the difference in costs and the horizontal line reflects the difference in effectiveness. The choice of treatment depends on the maximum amount of money that society is prepared to pay for a gain in effectiveness, which is called the ceiling ratio. Therefore, the bootstrapped ICERs will also be depicted in a cost-effectiveness acceptability curve showing the probability that MET-D (with and without feedback) is cost-effective using a range of ceiling ratios. Additionally, to demonstrate the robustness of our base-case findings a multi-way sensitivity analyses will be performed. In the sensitivity analysis uncertain factors of assumptions in the base case analysis will be recalculated in order to assess whether the assumptions have influenced the incremental cost-effectiveness ratio (ICER), for example by varying cost-prices and volumes between minimum and maximum [47].

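### The main depression outcome is set as unadjusted pre-post change, and nothing says which of two pre and two post HDRS ratings it uses

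*Protocol*

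**What the plan says.** Protocol section 7.1.1 gives the form of the outcome: "Main outcomes therefore are pre – post intervention change in i) depressive symptomatology". Section 9.2 gives the model in one sentence: "we will compare relevant pre, post and follow-up variables between the three groups using multilevel regression analyses". No baseline covariate and no common-baseline constraint appears in either place.

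Section 7.3 sets out when HDRS is rated:

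- After inclusion, subjects "undergo a psychiatric interview: HDRS". Section 3 places this rating at screening.
- After the baseline ESM week: "After this period, they undergo 2 psychiatric interviews (the depression part of the SCID-I and the HDRS").
- After the intervention: "Before and after the 5-day ESM period, all subjects again undergo the psychiatric interviews".
- Later: "follow-up measurements of SCID-I and HDRS take place at 4, 8, 12 and 24 weeks after the end of the intervention".

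Section 3 summarises the same schedule with one label for each side ("All groups receive the following pre and post intervention measurements"). Section 7.2 places randomisation after screening. It also acknowledges that the researcher who rates HDRS may know the participant's arm, and offers a comparison with the self-rated IDS as the check.

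**The concern.** There are two separate issues.

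**Precision.** If pre scores are modelled as outcomes alongside post scores, and each arm has its own baseline mean, the arm-by-time contrast from pre to post is a difference in mean change. That subtracts the whole of any chance baseline difference, whereas regression on baseline subtracts only the part that carries through to the post score. With 40 per arm, chance imbalance in HDRS is to be expected. A baseline HDRS is already collected in every participant, so the precision costs nothing to recover.

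**Definition.** Two pre and two post ratings allow 2 x 2 = 4 versions of pre-post change. Without a rule, the choice could be made after the data are seen, in a trial whose HDRS rater may not be blind.

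**Working it through.** **Inputs from the protocol.** 40 per arm, a 3-point HDRS-17 difference, alpha 0.05 and power 0.93 (section 4.4). The outcome form is in 7.1.1, the model in 9.2 and the rating times in 7.3.

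**Inputs not in the protocol (assumptions).** The SD s of a single pre rating, the pre-post correlation rho, the ratio k of post SD to pre SD, and the correlation between the two post ratings.

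**1. The stated power.** The 0.93 can be neither reproduced nor refuted, because no SD, correlation, sidedness or number of repeated measurements is given. Under a normal approximation (two-sided), the SD of the compared quantity must satisfy 3/(SD x sqrt(1/n1 + 1/n2)) = 1.960 + 1.476 = 3.436. This gives:

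- 40 v 40: SD = 3.90
- 40 v 80: SD = 4.51

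**2. Variance per subject.**

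- Change score: s²(k² + 1 − 2k·rho)
- Baseline-adjusted: s²k²(1 − rho²), ignoring the small cost of estimating the slope
- Difference: s²(1 − k·rho)²

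The difference is never negative. It is zero when k·rho = 1, that is, when the slope of post on pre is 1.

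**3. Variance ratio, adjusted to change score.** With k = 1 it reduces to (1 − rho²)/(2(1 − rho)) = (1 + rho)/2.

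| rho | k = 1 | k = 1.3 |
|---|---|---|
| 0.3 | 0.91/1.40 = 0.65 | 1.538/1.91 = 0.81 |
| 0.5 | 0.75/1.00 = 0.75 | 1.268/1.39 = 0.91 |
| 0.7 | 0.51/0.60 = 0.85 | 0.862/0.87 = 0.99 |

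The saving is therefore 15% to 35% with equal variances. If the post SD is 1.3 times the pre SD, it falls to 9% at rho 0.5 and 1% at rho 0.7.

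**4. Using both post ratings.** Let the post ratings correlate r with each other and rho with baseline, with k = 1. The adjusted variance of their mean is s²((1 + r)/2 − rho²). At rho = 0.5, relative to 0.75 for one post rating:

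- r = 0.7: 0.60/0.75 = 0.80
- r = 0.8: 0.65/0.75 = 0.87
- r = 0.9: 0.70/0.75 = 0.93

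**5. What this could mean for power (illustration only).** The calculation uses the noncentral t, 40 v 40, two-sided 0.05, 3 points, k = 1, one pre and one post rating, and leaves out the follow-up visits.

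| Assumed s | Change score, rho 0.3 / 0.5 / 0.7 | Adjusted, rho 0.3 / 0.5 / 0.7 |
|---|---|---|
| 5 | 0.61 / 0.76 / 0.93 | 0.79 / 0.86 / 0.96 |
| 6 | 0.46 / 0.60 / 0.81 | 0.64 / 0.72 / 0.87 |
| 7 | 0.36 / 0.47 / 0.69 | 0.51 / 0.59 / 0.76 |

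If the stated 0.93 is instead taken as the change-score power, adjusted power is Φ(3.436/√ratio − 1.960). With ratios 0.65, 0.75 and 0.85 this gives 0.989, 0.978 and 0.961, a gain of 3 to 6 percentage points.

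**6. Counting ratings.** Section 7.3 gives one rating at inclusion (screening in section 3), one after the baseline ESM week, one before and one after the post ESM week, and four at follow-up. Sections 3, 7.1.1 and 9.2 do not say which rating is pre and which is post. The time-frame figure is missing from the text reviewed here, so it is worth checking whether it settles this.

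**The case against.** The strongest reply is that much of this is silence. Section 9.2 does not say whether pre enters as an outcome or a covariate. A multilevel model with pre among the outcomes and a common baseline mean would fit the same sentence and be about as efficient as covariate adjustment. Covariates are often listed in an analysis plan, which is not at hand. This stands to the extent that the protocol does not exclude adjustment. But 7.1.1 does more than stay silent: it names change as the outcome, and 9.2 lists pre with post and follow-up as what is compared. The plain reading of the two together is an unadjusted change contrast.

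The size is also open to challenge, and fairly so. The simple ratio needs equal variances, the power table ignores the four follow-ups, and s and rho are assumed. Entry of residual cases requires a HAM-17 score above 7 (section 4.2), which may narrow the baseline spread and push k above 1, where the gain is smaller.

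A reader might infer three stronger points that the documents do not support:

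- *One post rating is thrown away.* Nowhere does the protocol say so. Section 4.4 bases power on repeated measurements, and the model in 9.2 can take both ratings. What is missing is the rule.
- *The change score is biased, for instance through regression to the mean.* Regression to the mean acts on all randomised arms alike and does not bias the contrast between them.
- *A change score is always less precise when rho is below 1.* Step 2 shows equality when the slope is 1.

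**Conclusion.** The point holds as one of efficiency and definition. As written, the main depression comparison is a valid contrast that is no more precise than the baseline-adjusted alternative and usually less so. Under equal variances and rho from 0.3 to 0.7, adjustment would cut the variance by 15% to 35%. With a post SD 1.3 times the pre SD, the cut is about 19%, 9% and 1% at rho 0.3, 0.5 and 0.7. The true size cannot be fixed from the protocol, and the power figures only illustrate it.

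The ambiguity over which pre and post ratings count rests on no assumption. It follows from setting 7.3 beside 7.1.1.

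No bias and no wrong figure is claimed. In particular, a reader might take the lower entries in the power table to show that 0.93 is wrong or that the trial is underpowered. They do not, since they depend on SDs the protocol does not give and leave out the repeated follow-up ratings.

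**What to change.** Revise sections 7.1.1 and 9.2 as follows:

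1. Model HDRS at post and at weeks 4, 8, 12 and 24, with arm, time and arm-by-time.
2. Adjust for HDRS rated before allocation and its interaction with time, or keep pre as an outcome and constrain its mean to be equal across arms.
3. Name the pre rating. The screening rating precedes randomisation under section 7.2. If randomisation also follows the baseline ESM week, say so, and both pre ratings can be used. If it does not, the second rating is made after allocation and should not serve as the baseline covariate.
4. Enter both post ratings as repeated occasions, and define the immediate effect as the arm difference averaged over the two.
5. Report raw change descriptively.
6. Treat IDS and empowerment the same way as far as their measurements allow. Section 7.3 schedules empowerment once before and once after the intervention, so only the baseline adjustment applies there.

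The cost is a few sentences of text. No visit, rating or patient burden is added.
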